### Methods in analysis to handle protocol non-adherence and any statistical methods to handle missing data {20c}

The main efficacy analysis will be via intention to treat with data from all participants included in the analysis including those who do not complete therapy. Every effort will be made to follow up all participants for research assessments, and the analysis will use, where appropriate, statistical techniques for handling missing data. All models will be estimated using maximum likelihood estimation, which allows for missing outcome data under the missing at random assumption; we may also use inverse probability weighting to adjust for non-adherence to allocated treatment and other intermediate outcomes as predictors of future loss to follow-up.

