Approximately 20 clinicians will be trained to deliver AVATAR therapy during the trial. This will include a core team of 8 trial therapists and clinicians at local NHS sites who will be trained with a view to delivering a smaller number of cases and building therapy and training capacity in the NHS. Training will involve initial orientation to the clinical and technical manuals followed by sessions (face-to-face or remote) focusing on the rationale, therapy targets and delivery of AVATAR-brief and AVATAR-extended. Initial pilot cases will be closely supervised by someone with experience of AVATAR therapy delivery. Training cases will be assessed for treatment fidelity and therapist competence using tools which have been developed for routine monitoring throughout the trial (see the ‘Strategies to improve adherence to interventions {11c}’ section). Therapy supervision during the trial will include individual and group-based supervision delivered from the main site (King’s College London) in addition to individual and peer-based supervision at each local site.

For both AVATAR-extended and AVATAR-brief arms, in-session measures assessing anxiety, perceived hostility, sense of presence and sensed presence will be completed at the end of each interaction with the avatar (items adapted from [26, 27]). The Working Alliance Inventory (WAI) Short-Form will be used to assess the quality of the therapeutic alliance from the perspective of the participant- this will occur at Session 4 (AVATAR-extended and AVATAR-brief) and repeated in Session 10 (AVATAR-extended only) if therapy delivery changes during the course of intervention (remote or face to face). Therapy process activities (e.g. between session phone contact or messaging and clinical team liaison) will be routinely collected to inform future implementation.

The AVATAR Therapy software [28] has been CE marked and registered with the MHRA as a class 1 medical device by Avatar Therapy Ltd. (www.avatartherapy.co.uk).

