## Statistical methods

### Statistical methods for primary and secondary outcomes {20a}

We will report all participant flow in the study in accordance with the CONSORT principles, with the 2018 extension for reporting social and psychological intervention trials ((CONSORT SPI) [31]). Descriptive statistics will be used to summarise assessments of recruitment, drop-out and completeness of therapy.

The primary outcome of voice-related distress as measured by PSYRATS-AH distress dimension score will be analysed using a mixed effects model including data from all time points. Fixed effects will be site, characterisation, baseline assessment for the outcome under investigation, random allocation, time and time*random allocation interactions. Participant and therapist will be included as random intercepts, with the participants in the TAU arm considered as being in individual clusters of size 1. Marginal treatment effects for each pairwise comparison will be estimated for outcomes at each time point and reported separately as mean adjusted differences in scores between the respective randomised groups with 96.5% confidence intervals and two-sided *p* values (to account for correlated multiple comparisons). For continuous secondary outcomes, the same approach will be followed, and for binary secondary outcomes, logistic mixed models will be used.

The random effect structure will account for repeated measures and clustering due to the partially nested design and allow estimates of separate ICCs in both randomised arms.

Cohen’s d effect sizes at 16 and 28 weeks will be calculated as the adjusted mean difference divided by the sample standard deviation of the outcome at baseline and displayed in a forest plot.

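### Fixing full maximum likelihood for all models modestly understates therapist variance and slightly narrows the 96.5% intervals, while REML is equally valid under missing at random

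*Protocol article*

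**What the plan says.** The estimator is set in the missing-data section of the protocol article, {20c}: "All models will be estimated using maximum likelihood estimation". The reason given there is that this copes with outcomes missing at random. REML is neither named nor excluded.

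The primary model is in {20a}. Its list of fixed effects opens "Fixed effects will be site, characterisation, baseline assessment for the outcome under investigation, random allocation, time and" and closes with the interaction of time and allocation. The random part reads: "Participant and therapist will be included as random intercepts, with the participants in the TAU arm considered as being in individual clusters" of size 1. The random-effect structure is also meant to "allow estimates of separate ICCs in both randomised arms". Results are to be given as "mean adjusted differences in scores between the respective randomised groups with 96.5% confidence intervals".

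On therapist numbers, {11a} says "Approximately 20 clinicians will be trained to deliver AVATAR therapy during the trial" and adds "This will include a core team of 8 trial therapists and clinicians at local NHS sites", the latter expected to take fewer cases each. Study setting {9} names four research sites. The document gives no therapist ICC and no caseload split, and does not say whether a therapist may treat at more than one site.

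**The concern.** ML estimates variance components as if the fixed effects were known. With many clusters this hardly matters. Here there would be about five therapists per site, or two per site if only the core team counts, and site is itself a fixed effect. Part of the between-therapist variation is absorbed by the site terms, and ML does not give it back. REML does.

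Two outputs are exposed. The first is the standard error of each therapy-versus-TAU contrast, and with it the 3.5% per-test level that the plan set for its two formal comparisons. The sample size contains no allowance for therapist clustering, so the analysis model alone has to deal with it. The second is the therapist ICC, which the plan wants to estimate and which later trials may use.

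The reason given for ML does not separate it from REML. Both are likelihood methods, and both are valid when outcomes are missing at random.

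**Working it through.** **1. The plan's own figures reproduce.** The correlation-adjusted level is 1 − 0.95^(1/2^(1−0.5)) = 0.0356, stated as 0.035. With d = 0.5, two-sided alpha 0.035 and 90% power, a plain two-mean calculation gives 92 per arm, hence 3 × 92 = 276, and 276/0.8 = 345. No design effect enters.

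**2. Direction and rough size.** If site effects were estimated from the therapy arms alone, ML would scale the between-therapist mean square by (therapists − sites)/therapists. That is (20 − 4)/20 = 0.80 with 20 therapists and (8 − 4)/8 = 0.50 with 8. This is only a guide: TAU participants also inform the site effects, and variance estimates are truncated at zero. Simulation is needed for the size.

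**3. Simulation.**
- From the protocol article: 92 analysed per arm, two follow-up visits, four fixed sites, TAU participants as singletons, nominal error 3.5%.
- Assumed: therapist ICC, participant variance half of the total, caseload pattern, therapists nested in site.
- Both estimators use a normal reference, so the comparison isolates the estimator.
- 4,000 runs per row. Monte Carlo standard error of the error rate is √(0.035 × 0.965/4000) ≈ 0.3 points.
- Error is 100% minus the coverage of the 96.5% interval.

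| Therapists | ICC | ML variance / true | REML variance / true | ML SE / REML SE | ML error | REML error |
|---|---|---|---|---|---|---|
| 20, equal caseload | 0.02 | 0.80 | 1.36 | 0.978 | 3.9% | 3.4% |
| | 0.05 | 0.72 | 1.05 | 0.973 | 4.7% | 4.0% |
| | 0.10 | 0.78 | 1.00 | 0.969 | 3.8% | 3.0% |
| 8 core with 70% of cases, 12 others | 0.02 | 0.69 | 1.30 | 0.974 | 4.1% | 3.6% |
| | 0.05 | 0.70 | 1.07 | 0.968 | 4.6% | 3.9% |
| | 0.10 | 0.75 | 1.00 | 0.965 | 4.8% | 4.1% |
| 8 only | 0.02 | 0.49 | 1.37 | 0.947 | 4.7% | 3.8% |
| | 0.05 | 0.55 | 1.07 | 0.933 | 5.6% | 4.5% |
| | 0.10 | 0.66 | 1.03 | 0.920 | 6.2% | 4.2% |

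A separate simulation, also with a normal reference for both estimators, gave with about 20 therapists ML errors of 3.7–4.7% against 3.3–3.9% for REML, ML standard errors 3–5% shorter, and an ML therapist ICC 18–39% below truth. With 8 therapists the ML error was 4.9–7.3% and the ICC 39–49% low.

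**4. Variants (20 therapists, equal caseload).**
- Separate therapist variances per therapy arm, as {20a} intends: ML/true is 1.24, 0.88, 0.83 and 0.85 at ICC 0.02, 0.05, 0.10 and 0.15. That is 12–17% low from 0.05 upwards, but too high at 0.02.
- Therapists crossing sites: ML/true is 1.05, 0.90 and 0.93 at ICC 0.02, 0.05 and 0.10, with standard errors under 2% shorter than REML.
- No therapist variance in TAU: ML/true is 0.78, 0.71 and 0.78, but the ML error is only 3.5%, 4.1% and 3.8%, against 3.2%, 3.5% and 3.3% for REML.

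**5. The remedy.** In further runs with 8 core therapists delivering 80% of cases and 12 others the rest, REML with Satterthwaite degrees of freedom rejected 3.1%, 3.7% and 3.5% at ICC 0.02, 0.05 and 0.10. ML with a normal reference rejected 4.1%, 4.5% and 4.7%.

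**The case against.** The sentence sits in a missing-data section and may be meant only to say that estimation is likelihood-based. The choice between ML and REML, and a degrees-of-freedom method, could well be settled in an analysis plan that is not shown. For degrees of freedom this stands: their absence from the article is not a fault. For the estimator it stands only in part. The article names ML for every model, and an analysis plan that follows it as written would use full ML.

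The effect is also small. With about 20 therapists the excess error is at most a little over one percentage point, and several individual rows lie within Monte Carlo noise of 3.5%. That is fair. The case rests on the consistent direction, since ML error exceeds REML error in every row, and on the absence of any gain from ML.

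A reader might infer more: that the therapist variance and the promised ICCs come out a third to a half too low as a rule, or that error control breaks down. The documents do not support this. A shortfall near half needs the 8 core therapists to deliver almost everything, whereas {11a} plans for local clinicians to treat as well. The arm-specific ICCs are 12–17% low, or too high when the true ICC is very small. Nesting in site is a natural reading but is not stated, and without it little bias remains.

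REML is not unbiased either. At ICC 0.01 to 0.02 its mean estimate is about 1.3 to 1.9 times the true value, because estimates cannot fall below zero.

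**Conclusion.** The point holds as a modest one. ML is a stated choice, the reason given does not favour it over REML, and this design is of the kind where it errs. Under nesting in site and a therapist ICC of 0.02–0.10, expect a therapist variance roughly 15–40% too low, 96.5% intervals about 2–5% too narrow, and a per-test error of about 3.7–4.8%, nearer nominal if TAU carries no therapist variance. About 5–7% error and a variance up to half too low apply only if 8 therapists deliver nearly all therapy.

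The ICC, the caseload split, the nesting and the normal reference are all assumptions, and the article fixes none of them. The direction for the primary intervals is anti-conservative. The size does not threaten the trial's conclusions unless a result is borderline.

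**What to change.** Replace the estimation sentence in {20c} with wording such as:

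> Linear mixed models will be estimated by restricted maximum likelihood, which is also valid when outcomes are missing at random, with Satterthwaite or Kenward-Roger degrees of freedom for tests and 96.5% confidence intervals. Logistic mixed models will be estimated by maximum likelihood. Therapist ICCs will be taken from the restricted maximum likelihood fit and reported with confidence intervals.

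Add a note that these ICCs will be imprecise and can be biased upward when the true ICC is very small. If the existing sentence was meant to cover REML, saying so resolves the point.

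The cost is a software option and a few words. Intervals become a few percent wider, and the design, data collection and sample size are untouched.

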### Health economic analyses

The use of services at baseline, 16 weeks and 28 weeks will be measured with the Client Service Receipt Inventory. Service costs will be calculated by combining these data with appropriate unit cost information (including NHS Reference Costs and figures from the University of Kent). These costs will be added to the costs of the therapy (based on staff time, overheads and activity levels). Costs will be compared between the three arms at 16 and 28 weeks using regression models adjusting for baseline differences. (The 28-week comparison will be of the cumulative costs to that time point.) Bootstrap methods will be used to generate confidence intervals around the cost differences. Quality-adjusted life years (QALYs) will be generated using the EQ-5D-5L along with cross-walk method recommended by NICE. We will assume linear change between time points and use area under the curve methods. QALY comparisons will make adjustment for baseline EQ-5D-5L tariffs. Cost-effectiveness will be assessed by generating incremental cost-effectiveness ratios (in the event of non-dominated arms) and uncertainty addressed using cost-effectiveness planes and acceptability curves. Missing cost and EQ-5D-5L data will be imputed using multiple imputation methods on 1000 bootstrapped resamples. We will assume that data are missing at random. The imputation will be conducted on each bootstrapped resample in turn and cost-effectiveness estimates made on each.

#### Plans to give access to the full protocol, participant level-data and statistical code {31c}

The datasets generated and/or analysed during the current study will be available in anonymised form, and the corresponding statistical code, from the research team on reasonable request, subject to review, following the publication of trial results.

## Oversight and monitoring

### Composition of the coordinating centre and trial steering committee {5d}

The trial has been carefully designed to ensure compliance with Good Clinical Practice and scientific integrity. The research programme development, design and implementation will be managed by the Chief Investigator (CI) and the co-applicants, in consultation with service-user consultants and other expert research collaborators from within and outside of the CI's institution. A dedicated Trial coordinator post will assist in the day-to-day management of the project reporting to the (CI). A trial management committee (TMC) will meet monthly, its membership will include the investigators and the Trial coordinator and site coordinators. It will be chaired by the CI and will manage the day–to-day running of the study and ensure good communication between trial sites, receiving monthly reports from each site on recruitment, therapy completion, adverse events, reviewing progress against milestones and finding solutions to problems as they arise. It will oversee the preparation of reports to the Trial Steering Committee (TSC) and Data Monitoring and Ethics Committee (DMEC).

The Clinical Trial Steering Committee (TSC) will meet at least every 6 months. Its purpose is to provide overall supervision of the trial, approving the protocol and amendments, monitoring adherence to the protocol and providing independent advice on all aspects of the trial. A senior clinical academic, independent of the trial team, will be nominated as the chair. The TSC will include senior clinicians, clinical academics and two service users of mental health services with lived experience of psychosis. The principal investigator (the co-applicant lead at each site), co-applicant investigators, trial coordinator and representatives for each clinical site may join the meetings as observers. The Wellcome Trust may appoint up to two representatives who shall have the right to attend TSC meetings in person, by telephone or by other electronic means as observers. Wellcome observers have no right to participate in the decisions of the TSC.

### Patient and Public Involvement (PPI) strategy

Each of the four sites will have a local PPI reference group who will attend regular meetings and be asked to contribute to the delivery of the trial in a range of ways, e.g. reviewing materials, supporting recruitment and dissemination and piloting assessment protocols. These local reference groups will be brought together in annual whole trial PPI meetings with input from expert consultants to ensure effective PPI in AVATAR2. We will also develop and deliver the quantitative interviews with input from these consultants and in collaboration with members of the local PPI reference groups.

#### Composition of the data monitoring committee, its role and reporting structure {21a}

A DMEC will be convened and will meet at least annually and report to the TSC. It will have access to all unblinded trial data and will receive regular reports on adverse events. The DMEC will be notified of any serious adverse events as they occur and will consider whether any interim analyses are warranted, review data (including numbers of participants stratified at each level) and advise the TSC on any ethical or safety reasons why the trial should be prematurely ended. The DMEC chair will be responsible for confirming judgements on the likelihood of any SAE’s relatedness to Clinical Trial involvement as well as the SAE’s intensity and unexpectedness. Membership of the DMEC will be independent of the applicants and of the TSC. An independent senior clinical academic will be appointed as chair and the group will also comprise another independent senior clinical academic and a senior statistician. The CI, trial coordinator and the trial statistician will attend parts of the DMEC meeting to provide reports but will not be members of the DMEC or be present when unblinded data is discussed.

#### Adverse event reporting and harms {22}

The occurrence of adverse events (AEs) will be monitored actively and systematically, following guidance from the Consolidated Standards of Reporting Trials (CONSORT) with the extension for social and psychological interventions, and the extension for reporting of harms. Medical Research Council Guidelines for Good Practice in Clinical Trials will also be followed to ensure good governance of the trial for integrity and participants’ safety and wellbeing.

AEs are defined as any untoward medical occurrence, unintended disease or injury, or untoward clinical signs in service user/patient participants, whether or not related to the therapy or device which require additional support or input from health professionals.

Adverse events will be initially assessed at three levels of intensity: mild, moderate and severe, which reflect the impact of the event on the person at the time. Please note there is a distinction between ‘severe’ and ‘serious’. Seriousness is the criteria for defining regulatory reporting obligations and the following will be considered as serious adverse events (SAE, categories A–C): All deaths (category A), incidents which acutely jeopardise the health or psychological wellbeing of the individual, resulting in immediate hospital admission and/or permanent disability (category B), or resulting in injury requiring immediate medical attention (category C). These SAEs will include but are not limited to (1) hospital admissions; (2) home treatment team involvement; (3) suicide attempts; (4) any violent incident necessitating police involvement (whether victim or accused); (5) self-harming behaviour; and (6) all deaths. In order to ensure active surveillance of harms, at each assessment point, research workers will utilise the interview to actively check for the occurrence of specific AEs. At the completion of the trial, all medical notes will be checked, for the total duration of enrolment, for any previously undisclosed record of AEs. Reasons for withdrawal from the study will also be recorded.

The chair of the DMEC will determine relatedness of the event to the research assessment, therapy or device based on a temporal relationship, and consideration of whether there were insufficient or inadequate instructions for use, deployment, installation, or operation, or any malfunction of the AVATAR software. An adverse event may also be device-related if it was the result of user error or intentional misuse of AVATAR therapy software. The DMEC chair will confirm whether the event is unexpected or unexplained given the participant’s clinical course, previous conditions and history, and concomitant treatments. As detailed in the risk analysis conducted for the CE-marking of AVATAR therapy software, we do not anticipate any serious adverse device effects. We do not anticipate any serious therapy or assessment-related adverse events; this expectation is based on the safety data from the previous AVATAR trial.

All SAEs will be reported immediately to the Chief Investigator and Principal Investigators (for the relevant site) and the independent chair of the Data Monitoring and Ethics Committee (DMEC). At each meeting of the DMEC, or at any time at the request of the DMEC Chair, a full report of AEs will be reviewed.

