### Intervention description {11a}

AVATAR-brief consists of six individual, face-to-face sessions (in addition to an initial clinical assessment session including avatar creation), delivered by trained therapists (with previous experience working in psychosis), assisted by the avatar software described previously. Therapy focuses on the exposure/assertiveness component and will follow detailed session-by-session guidance in a written AVATAR clinical manual. At the end of each interaction with the avatar, the therapist will return to the room and support the participant to answer questions regarding their experience of the interaction (perceived hostility, anxiety, sense of voice presence) presented either on the screen or in a booklet (at therapist’s discretion).

AVATAR-extended consists of twelve individual, face-to-face sessions (in addition to the initial assessment and avatar creation session), delivered by trained therapists, assisted by the AVATAR therapy software described previously. It includes both phases of treatment as described earlier and detailed in the AVATAR clinical manual. The participants will also complete the same questions at the end of each interaction with the avatar as described above. In line with the clinical manual, the number of sessions for both AVATAR-brief or AVATAR-extended is permitted to vary by no more than two sessions added or removed; any such change will be guided by the clinical judgement of the therapist and in collaboration with the participant.

It is necessary to have access to two private rooms to conduct the therapy; additional equipment includes a laptop (with a webcam and microphone) and secure network, the AVATAR therapy software and the participant must have access to a device on which they can listen to recordings of the sessions (this will be provided by the study team as required). Face-to-face sessions will mostly be conducted at a clinical research facility or local clinical team settings.

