### Criteria for discontinuing or modifying allocated interventions {11b}

Apart from the change in number of sessions (plus or minus 2) described above, to take account of clinical circumstances, the intervention may be discontinued if the participant requests this or if the clinician judges, in consultation with the wider supervisory team, that the intervention is associated with a significant worsening of mental health. In this case an Adverse Event form would also be completed. It will be made clear to each participant that, should they find any aspect of the research distressing, including the intervention, and/or no longer wish to continue, they will be able to withdraw without this impacting on their usual clinical care in any way.

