#### Frequency and plans for auditing trial conduct {23}

The roles of the TSC and the DMEC are to ensure the trial is conducted to a high standard; these committees are independent from the investigators and sponsor. The DMEC will receive open reports showing summary measures of the data across the sample and will be the only committee to receive closed reports displaying summary measures of the data split by treatment group.

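### Adverse events may be ascertained unequally between arms: one reporting route exists only with therapy, and the notes check common to all arms comes after the DMEC's in-trial by-arm reports

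*Protocol article*

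**What the plan says.** All references are to the protocol article.

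- **Definition.** Under Adverse event reporting and harms {22}, an untoward event is an AE "whether or not related to the therapy or device which require additional support or input from health professionals". No arm is named.
- **Routes open to all arms.** The same section says that "at each assessment point, research workers will utilise the interview to actively check for the occurrence of specific AEs". It adds: "At the completion of the trial, all medical notes will be checked, for the total duration of enrolment, for any previously undisclosed record of AEs". Under Who will be blinded {17a}, these research workers are blind to allocation.
- **Route open only with therapy.** Under Criteria for discontinuing or modifying allocated interventions {11b}, therapy may be stopped if the clinician judges "that the intervention is associated with a significant worsening of mental health". The text continues: "In this case an Adverse Event form would also be completed".
- **Extra contact with therapy.** Intervention description {11a} plans 6 or 12 sessions, each course preceded by one assessment and avatar-creation session, with up to two sessions added or removed. Process activities such as "between session phone contact or messaging and clinical team liaison" are logged, for the stated purpose of informing implementation.
- **Use of the data.** The DMEC meets at least annually, receives regular AE reports and may advise early termination on safety grounds {21a}. It alone receives "closed reports displaying summary measures of the data split by treatment group" {23}.

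**The concern.** A comparison of AE counts between randomised arms is fair only if an event has much the same chance of being recorded in each arm. Here a participant in therapy meets a trial clinician repeatedly between baseline and week 16, and one AE form is tied to an action that cannot occur in TAU. A TAU participant has no scheduled trial-clinician contact in that interval.

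The definition adds an uncertainty. It turns on whether a health professional had to give extra support, and Eligibility criteria {10} describes the therapists as mental health clinicians. The article does not say whether a therapist's own additional input meets the definition. If it does, the same episode of distress qualifies more readily in the therapy arms.

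At stake is how the by-arm safety data are read. An excess under therapy could be partly an artefact of closer observation. Equally, a genuine excess would be hard to tell from such an artefact if the source of each event is not known. The in-trial DMEC reports are most exposed, because the notes check that would do most to level the arms has not yet been made.

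**Working it through.** The protocol states no AE rate, capture rate or safety threshold, so there is no figure to reproduce. Two checks are possible.

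**1. Scheduled staff contacts from randomisation to week 28.** Every arm has 2 post-randomisation assessments. Each therapy arm adds 1 initial session plus its course, which may vary by 2.

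| Arm | Planned | With the permitted variation |
|---|---|---|
| TAU | 2 | 2 |
| Brief | 2 + 1 + 6 = 9 | 7 to 11 |
| Extended | 2 + 1 + 12 = 15 | 13 to 17 |

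The extra planned clinician sessions are thus 7 and 13. The count leaves out ESM debrief meetings, any remote set-up session and all usual-care contact. It measures opportunity to notice an event; it does not measure bias.

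**2. Effect of unequal capture when true risk is equal.** Let p be the true risk, c the share of events caught by the routes common to all arms, and e the share of the remainder caught only through therapy contact. Both c and e are assumptions.

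- Recorded risk in TAU = p × c
- Recorded risk with therapy = p × [c + e(1 − c)]
- Spurious risk ratio = 1 + e(1 − c)/c, which does not depend on p

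| c | e = 0.25 | e = 0.5 | e = 0.9 |
|---|---|---|---|
| 60% | 1.167 | 1.333 | 1.600 |
| 80% | 1.063 | 1.125 | 1.225 |
| 95% | 1.013 | 1.026 | 1.047 |

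In participants, with the planned 115 per arm, an assumed p of 40% and e = 0.5:

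- c = 60%: TAU 115 × 0.40 × 0.60 = 27.6, about 28; therapy 115 × 0.40 × 0.80 = 36.8, about 37.
- c = 95%: TAU 115 × 0.40 × 0.95 = 43.7, about 44; therapy 115 × 0.40 × 0.975 = 44.9, about 45.

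The result depends mainly on c. During the trial c rests on the interviews and on immediate reporting of serious events. At the end it also includes the notes check and should be higher.

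**The case against.** The case on the other side is substantial.

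- **The common routes are good ones.** Blinded interviewers ask actively about AEs, and the notes are checked for the whole of enrolment. An AE by definition needs professional input and every participant is under a specialist team, so qualifying events are likely to reach the notes. This stands for the final comparison and for deaths and admissions. It does not help reports made before the notes check, and the interviews may be lost for participants who withdraw (20% attrition is allowed for).
- **Therapy sessions are not named as an AE source.** Apart from the form completed when therapy is stopped for worsening, this is correct. The contact counts of 9 and 15 against 2 therefore cannot be read as multipliers of AE detection.
- **The DMEC is independent, includes a statistician and works to no stated AE threshold.** This limits the consequences, but members cannot allow for the source of an event if it is not recorded.
- **Form fields and table layout belong in documents not shown.** This is fair as to their absence. The point rests instead on what the article does fix: the therapy-only form, the timing of the notes check and the by-arm reporting.
- **Separating events by source can mislead in the other direction.** The notes check looks for events not already disclosed. If only the first source were kept, events that a therapist reported first would drop out of a common-route comparison even when interviews or notes would also have found them, and harm from therapy would be understated. This stands in full and shapes the fix.

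A reader might also infer that the therapy arms have a looser AE trigger. The text does not support that: the definition is the same for all arms, and the section on stopping therapy does not say that worsening is recorded only then. Worsening in TAU that needs professional input is an AE too.

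**Conclusion.** There is a real risk of unequal AE ascertainment, mainly for non-serious events and for the DMEC's in-trial reports. Serious events are less exposed, although self-harm, which is listed among them, may come to a therapist's attention without any service contact. The likely direction is over-recording of harm in the therapy arms, potentially more so for extended than for brief.

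The size is unknown. Under equal true risk, common-route capture of 60% to 95% and therapy-only capture of 25% to 90% of the remainder, the spurious risk ratio lies between about 1.01 and 1.6. All of these capture rates are assumptions.

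Two stronger conclusions are tempting and not supported. One is that the safety comparison is shown to be biased: with nearly complete common routes the distortion is negligible, and the document does not say how complete they are. The other is that the trial cannot tell whether therapy worsens mental health relative to TAU: PSYRATS-AH distress and the other symptom outcomes are measured in all three arms at 16 and 28 weeks, with blinded assessors.

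**What to change.** 1. On each AE form, record every source that identified the event (interview, notes, therapist, other), not only the first.
2. Carry out the interview and notes checks in the same way in all arms, whether or not an event has already been reported, so that an event known from a therapist can also be credited to a common route.
3. In the DMEC closed reports and the final report, keep the all-source AE and SAE table by arm. Beside it, add a by-arm comparison of events found by the common routes, with therapist-only events listed separately.
4. State whether a therapist's own additional input counts as health-professional input under the AE definition.
5. Optionally, tabulate worsening from baseline on PSYRATS-AH distress identically in all three arms, using a pre-stated margin beyond measurement noise. Counting any rise, however small, would mix noise with deterioration.

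The cost is one multi-select field, a somewhat fuller notes check and a few extra table columns. No safety information is removed.
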